### Primary outcomes

The primary outcome will be a significant reduction in the self-reported MFI-20 score during modafinil treatment compared to that participant’s difference during the placebo period.

### Secondary outcomes

Secondary analyses will assess the effect of treatment with 200 mg modafinil daily to baseline assessments of cognition (MoCA), mood (DASS 42) and quality of life (SSQoL). We will also seek a repeated measure of fatigue with the FSS which is used more widely yet is much less specific for the source of type of fatigue.

Secondary analysis will also explore the MRI changes associated with administering 200 mg modafinil daily in terms of cerebral blood flow on ASL and brain activity on rsfMRI.

### MRI analysis plan

Secondary analysis will be performed on unblinded patient data to compare with MRI findings. Resting state functional MRI (rsfMRI) data will be analysed using independent component analysis to determine whether there are different network activation patterns on active drug or placebo. Arterial spin labelling (ASL) will also be analysed to determine whether there are any changes in the whole brain cerebral blood flow between when participants are on active drug or placebo. Lastly, the SSQoL, MoCA, DASS 42 and MFI-20 will be analysed in conjunction with rsfMRI data to identify whether a change in any score is associated with alterations in resting state network function.

### Statistical analysis plan

A linear mixed model will be used to detect a significant difference between final MFI-20 scores during each period as the outcome. The value of the baseline MFI-20 score at trial start and after crossover will be used as a covariate, and a group variable as the exposure of interest in order to correct for changes in baseline MFI-20 scores; an order term will also be included to make sure that there is no carryover effect, i.e. no difference in effect if the active drug or placebo is given first.

Secondary outcomes will be assessed using the same methods as for the MFI analysis but using the MoCA, DASS42, SSQoL and FSS instead. MRI analysis will be undertaken using the same methods as for the primary analysis.

Given that all secondary outcomes are also continuous, the same approach will be used for analysis of these outcomes.

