### Assessments

Assessments will be carried out at baseline, in the last week of the first 6-week treatment arm, after a 1-week washout period and in the last week of the second 6-week treatment arm (Fig. 1). The assessment at each time point will include the MFI-20, the Montreal Cognitive Assessment (MoCA), the Fatigue Severity Scale (FSS), the Depression, Anxiety and Stress Scale (DASS 42) and the Stroke-specific Quality of Life (SSQoL) scale. All assessments will be carried out by research staff blinded to treatment. All participants will also complete magnetic resonance imaging (MRI) sessions at baseline, crossover and study conclusion to measure cerebral blood flow on arterial spin labelling (ASL) and brain activity on resting state functional MRI (rsfMRI). Drug adherence will be monitored through tablet return for each patient in each strata (placebo or active drug).

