### Sample size

The study was designed to have 80 % power in detecting a 10 point decrease in self-reported fatigue on the MFI after 6 weeks of modafinil treatment with a type I error rate of 0.05 and assuming standard deviation in the patient population of 14. Using previously reported effects of modafinil on fatigue for stroke survivors [10], multiple sclerosis [12] and a Cochrane review [13] a total sample size of 34 is required for a crossover study. Assuming modest participant dropout and study drug compliance, we aim to recruit 36 participants in total. The crossover design reduces the number of participants required and the negative effects of missing data given the small number of dropouts expected [14].

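### A single slope for the period-specific MFI-20 baseline is dominated by between-person differences and costs precision at moderate or higher within-person correlation; separate slopes are a cheap improvement

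*Protocol article*

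**What the plan says.** All references are to the protocol article.

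- **Statistical analysis plan.** The outcome is the final MFI-20 score of each period, analysed in a linear mixed model with a group term and an order term. On the baseline: "The value of the baseline MFI-20 score at trial start and after crossover will be used as a covariate". The stated purpose is to correct for changes in baseline. The same method is carried over to MoCA, DASS 42, SSQoL and FSS.
- **Assessments.** After the baseline visit and the end of period 1, scores are taken "after a 1-week washout period and in the last week of the second 6-week treatment arm". The second baseline therefore falls about 1 week after the period 1 final score and about 6 weeks before the period 2 final score.
- **Primary outcomes.** The reduction during modafinil is compared with the same participant's "difference during the placebo period". This reads as a comparison of within-period changes, whereas the analysis section compares final scores.
- **Sample size.** "The study was designed to have 80 % power in detecting a 10 point decrease in self-reported fatigue", "with a type I error rate of 0.05" and "assuming standard deviation in the patient population of 14"; from this "a total sample size of 34 is required for a crossover study", with 36 to be recruited. No within-person correlation is given, and no allowance for the baseline term is mentioned.

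**The concern.** In a two-period crossover the treatment effect is estimated from differences within a participant. A baseline helps that contrast only so far as the difference between a participant's two baselines predicts the difference between the two final scores. A random-intercept model with one slope does not estimate that relation alone. It also uses the relation between participants, which is strongly positive because people who are more fatigued tend to score high at every visit.

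The schedule gives little reason to expect an equally strong within-person relation, since the second baseline lies closer in time to the period 1 outcome than to the period 2 outcome it is meant to adjust. If the fitted slope is too steep, part of the random variation in the baselines is subtracted from the treatment contrast. At stake are the width of the confidence interval and, depending on what the SD of 14 means, the stated power. The same would apply to the four questionnaire secondary outcomes.

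**Working it through.** **Inputs.** From the Sample size section: difference 10 points, SD 14, type I error 0.05 (two-sided assumed), 34 required, 36 recruited. Assumed, because the article gives no value: equal correlation *r* between all four MFI-20 scores, shown over a range.

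**Step 1: the plan's own figure.** Take the SD of the within-person difference as 14 × √2 = 19.8. A two-sided t-test then needs 33 participants, or 34 when made even for two sequences. Power is 81.5% at 34 and 83.7% at 36. So 34 is reproduced for a plain contrast of final scores. An SD of the difference of 14 would need only 18. The value 19.8 arises in two ways: 14 is the within-person SD, or 14 is the total SD and the correlation is zero.

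**Step 2: the slopes.** Write each participant's data as sums and differences over the two periods, with unit variances.

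- Between persons: Cov(sum of finals, sum of baselines) / Var(sum of baselines) = 4r / [2(1 + r)] = 2r / (1 + r).
- Within persons: Cov(difference of finals, difference of baselines) = r − r − r + r = 0, so the correct slope is 0.
- Single slope *b*, large-sample likelihood: minimise log[2(1 + r) − 8rb + 2(1 + r)b²] + log[2(1 − r)(1 + b²)].
- Effect on the treatment contrast: variance is multiplied by 1 + b².

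For r = 0.5, the between slope is 0.667, b = 0.442 and the factor is 1 + 0.442² = 1.20.

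**Step 3: against separate slopes.** Estimating the within-person slope separately costs about 1/30, or 3%, in variance at N = 34 (factor 1.033). For r = 0.5 the ratio is 1.196 / 1.033 = 1.16.

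| r | between slope | single slope b | variance vs no baseline | variance vs separate slopes |
|---|---|---|---|---|
| 0.2 | 0.33 | 0.18 | ×1.03 | ×1.00 |
| 0.3 | 0.46 | 0.26 | ×1.07 | ×1.03 |
| 0.5 | 0.67 | 0.44 | ×1.20 | ×1.16 |
| 0.7 | 0.82 | 0.66 | ×1.44 | ×1.39 |

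**Step 4: power of the single-slope model (difference 10).**

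| r | 14 = within-person SD, N = 34 | same, 36 completers | 14 = total SD, N = 34 |
|---|---|---|---|
| 0 | 81% | 84% | 81% |
| 0.2 | 80% | 83% | 88% |
| 0.3 | 79% | 81% | 91% |
| 0.5 | 74% | 77% | 96% |
| 0.7 | 66% | 69% | 99% |

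With separate slopes and 14 as the within-person SD, power at 34 is about 80% at every r. Simulation of the mixed model at N = 34 agrees: 78.9%, 74.5% and 66.6% for the single slope at r = 0.3, 0.5 and 0.7. The mean estimate is about −10 and null rejection is about 5 to 6%.

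**Step 5: other correlation patterns.**

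- If correlation decays with time as 0.4 + 0.4·exp(−weeks/10), the within-person slope is −0.04, the single slope 0.59 and the variance factor 1.40.
- If the baseline and final score of the same period share 0.2 extra correlation, the within-person slope is 0.2 / (1 − r), that is 0.29 at r = 0.3 and 0.40 at r = 0.5. The single slope then gives variance factors of 0.96 and 0.92. Separate slopes give [1 − 0.29²] × 1.033 = 0.95 and [1 − 0.40²] × 1.033 = 0.87.

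**The case against.** **The model is inferred.** The article gives no equation or covariate coding, and both baselines could be meant as participant-level covariates. They would then cancel from the within-person contrast and do no harm. This is a fair caution. But two participant-level values could not correct the contrast for a change between baselines, which is the stated aim, so one period-varying covariate is the more natural reading. The choice of covariate is stated, not left open.

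**Power.** A reader might infer that the trial is underpowered. The article does not support that. It describes 14 as an SD in the patient population, which in plain words is a total SD. The figure of 34 also follows from a total SD of 14 with zero correlation, a conservative calculation. On that reading the single-slope model keeps 81% to 99% power. Even with 14 as the within-person SD, falling below 80% needs a correlation above about 0.2 at 34, or somewhere between 0.3 and 0.5 with 36 completers. This objection stands.

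**Worse than no baseline.** A reader might infer that the planned covariate always does harm. It does not: with 0.2 extra same-period correlation it beats leaving the baseline out. At r = 0.3 and 0.5 it remains about 1% and 6% behind separate slopes. At low correlation the extra degree of freedom cancels the gain from separating.

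**Change scores.** A reader might infer from the Primary outcomes section that changes will be analysed directly. Under equal correlation that would double the variance and give about 52% power at 34, with 14 as the within-person SD. The analysis section plans no such analysis: it models final scores. What remains is a mismatch of wording.

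**Conclusion.** The point holds as a matter of precision, not validity. On the natural reading, the single slope is pulled towards the between-person relation and over-adjusts the treatment contrast. Under equal correlation of 0.3 / 0.5 / 0.7 this costs about 7% / 20% / 44% in variance against no baseline, and about 3% / 16% / 39% against separate slopes. These figures rest on an assumed correlation and its pattern. There is no net gain from separating at about 0.2 or below, and only a small one if same-period scores are more closely related. Loss of the stated 80% power is possible only if 14 is a within-person SD, and the article does not say that it is. This is a cheap improvement to an otherwise valid analysis.

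**What to change.** 1. In the Statistical analysis plan section, replace the single period-specific baseline by two covariates with separate slopes: the participant's mean of the two baselines, and each period's deviation from that mean. Apply this to the MFI-20 and to FSS, MoCA, DASS 42 and SSQoL.
2. In the Primary outcomes section, word the outcome as the modafinil-minus-placebo difference in final MFI-20 score, so that it matches the analysis.

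The cost is one sentence in each section, and one degree of freedom, about 3% in variance if the within-person slope is truly zero. No new data, visits or participants are needed. The change should be recorded before unblinding. Stating in the Sample size section which SD the 14 is would also settle the power question.

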### Therapy

Participants will be randomised 1:1 to modafinil 200 mg per day or placebo. All participants will be provided with 6 weeks’ worth of study drug after randomisation. After 6 weeks, participants will be asked to return to the study centre for assessments and to return study drug bottles to assess compliance. After the study drug has been returned, participants will have a 1-week washout period. Once the washout period has been completed, participants will again be asked to return to the study centre and crossover will occur where participants who initially received modafinil will be given a placebo or those who were given placebo will receive modafinil. Lastly, after 6 weeks on the second round of the study drug, participants will be asked to return to the study centre for assessments and to return study drug bottles to assess compliance.

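### A non-significant order term cannot show that carryover is absent, and the post-washout baseline covariate can bias the treatment estimate in a direction that depends on how long any carryover lasts

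*Protocol article*

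**What the plan says.** The protocol's Statistical analysis plan section analyses the end-of-period MFI-20 by a linear mixed model. On the covariate it states: "The value of the baseline MFI-20 score at trial start and after crossover will be used as a covariate". On carryover it states: "an order term will also be included to make sure that there is no carryover effect", explained as the effect not depending on which treatment comes first.

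Under Therapy, after the first 6-week period, "participants will have a 1-week washout period". The Assessments section places the second baseline after that washout and the last assessment in the final week of the second 6-week period.

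The Sample size section covers the treatment effect only: "80 % power in detecting a 10 point decrease in self-reported fatigue", "with a type I error rate of 0.05" and "assuming standard deviation in the patient population of 14". It concludes that "a total sample size of 34 is required for a crossover study" and "we aim to recruit 36 participants in total". It gives no power for the order term. The same model is planned for the secondary outcomes and the MRI measures.

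**The concern.** Two features of the model bear on carryover.

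1. The order term is a comparison between the two sequence groups, in a trial sized for a within-participant comparison. The protocol nevertheless credits it with establishing that carryover is absent. If it has little power, its usual result is non-significant whatever the truth, and a statement of no carryover would rest on nothing.
2. The second baseline follows a full treatment period and only one week off drug, so it is a post-treatment value. If some drug effect remains in it for those who took modafinil first, adjusting for it moves the treatment estimate itself. The same adjustment can also hide the signal that the order term is meant to detect.

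At stake are the carryover statement in the trial report and the size of the reported effect, for the primary outcome and for every outcome analysed the same way.

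**Working it through.** **Inputs.** From the protocol: alpha 0.05 (sidedness not stated, two-sided assumed), effect 10, SD 14, N = 34 required and 36 recruited, 1:1 allocation. Not in the protocol, so assumed and shown as ranges: between-period correlation rho, baseline slope beta, carryover size.

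**Reproducing the plan's figure.** Take 14 as the within-participant SD (or rho = 0), so the SD of a within-participant difference is 14 × √2 = 19.8. A two-sided crossover t-test with N − 2 degrees of freedom gives power 0.815 at N = 34. The stated 34 reproduces.

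**Order term without covariates.** Let λe be the carryover still present in the period-2 final score. The sequence means differ by λe/2, with

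SE = 14 × √((1 + rho)/2) × √(4/N).

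At N = 34 and rho = 0.5: 12.1 × √(4/34) = 4.16. The 95% half-width for λe is 2 × t × SE.

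| N | rho | SE | Power, 5 points | Power, 10 points | 95% half-width for carryover |
|---|---|---|---|---|---|
| 34 | 0 | 3.40 | 11% | 30% | 13.8 |
| 34 | 0.7 | 4.43 | 9% | 20% | 18.0 |
| 36 | 0 | 3.30 | 11% | 31% | 13.4 |
| 36 | 0.7 | 4.30 | 9% | 20% | 17.5 |

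At N = 34, 80% power needs a carryover of about 20 to 26 points. These figures favour the plan: if 14 is the within-participant SD and rho is 0.5, the total SD is about 19.8 and power falls to about 7% for 5 points and 13% for 10.

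**Effect of a period-specific baseline.** Let τ be the true treatment effect and λb the carryover in the post-washout baseline (negative values mean benefit). In the modafinil-first sequence the expected final scores are τ then λe; in the other sequence, 0 then τ. The within-participant contrast gives [(τ − λe) + τ]/2 = τ − λe/2. Adjusting for a baseline that has moved by λb in the modafinil-first sequence adds beta × λb/2:

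- treatment estimate = τ − λe/2 + beta × λb/2
- order term = (λe − beta × λb)/2

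Example with τ = −10, λb = −5, λe = 0, beta = 0.43: −10 − 1.1 = −11.1.

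The planned model (random intercept, REML, with period, treatment, order and period baseline) was simulated with N = 34, SD 14, true effect −10, four correlation structures and 800 runs per scenario. Fitted beta was about 0.4 to 0.65.

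| Carryover at second baseline, then at final score (points) | Planned model | Trial-start baseline only |
|---|---|---|
| 5, 0 | −11.0 to −11.7 | about −10.0 |
| 10, 0 | −12.1 to −13.3 | −10 (formula) |
| 5, 2.5 | −9.8 to −10.4 | −10 + 1.25 = −8.75 (formula) |
| 5, 5 | −8.6 to −9.1 | about −7.5 |
| 10, 10 | −6.9 to −8.2 | about −5.0 |

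In the planned model the order term was significant in 2-10% of runs for carryover up to 5 points and in 9-22% for 10 points. With 5 points at baseline and 2.5 at the end it was significant in 2-5%, because the two parts of its expectation nearly cancel.

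**A more direct check.** The post-washout score compared by sequence estimates λb itself, not half of it. For change from trial start, SE = 14 × √(2(1 − r)) × √(4/N). At N = 34 this is 4.80 (half-width 9.8) for r = 0.5 and 3.72 (7.6) for r = 0.7. Adjusting for the trial-start score instead, SE = 14 × √(1 − r²) × √(4/N): 4.16 (8.5) and 3.43 (7.0). The half-width is thus about 7 to 10 points, against about 13 to 18 for the order term. Power of the change score for 5 points is still only 17-26%. The two checks look at different times: this one at the end of washout, the order term at the final score.

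**The case against.** A reader might infer that the second-baseline covariate inflates the modafinil effect as a rule, and that the primary model should therefore use the trial-start score only. The protocol does not support that.

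- Exaggeration requires beta × λb to be larger in size than λe. If carryover persists in full, the planned model attenuates the effect, and dropping the second baseline attenuates it more (about −7.5 against −8.6 to −9.1 for 5 points).
- Nothing in the protocol shows that one week of washout is too short. If it suffices, this bias is zero.
- The covariate sentence can also be read as both baselines entering at participant level. The treatment estimate then stays at about −10.0 when carryover is in the second baseline only. Period-specific entry is the likelier reading, given the stated aim of correcting for changes in baseline, but it is not certain.
- Dropping the second baseline can cost precision. At a within-period correlation of 0.7 the SE rises from 2.30 to 2.59, equivalent to (2.59/2.30)² = 1.27 times the participants. At 0.6 it falls slightly, from 2.47 to 2.38.

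All of this stands, and it rules out replacing the primary model. It is also fair that the protocol states no action triggered by the order term, so it contains no two-stage testing rule to criticise.

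None of this rescues the claim made for the order term. Reading it as a treatment-by-order difference does not help either: in a 2×2 crossover that contrast mixes twice the period effect with the carryover.

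**Conclusion.** The order term cannot do what the protocol says it does. With SD 14 and correlations of 0 to 0.7, its power is about 9-11% for 5 points of carryover and 20-31% for 10, and its interval for carryover is about ±13 to ±18 points, wider than the 10-point target effect. This conclusion holds across the whole assumed range.

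The covariate point is conditional. If the baseline is period-specific and the washout incomplete, a true −10 could be estimated anywhere from about −6.9 to −13.3 over carryovers of up to 10 points, in either direction or with almost no bias, depending on persistence. The carryover sizes, slopes and correlations are assumptions, and the protocol gives no figure that would choose among them. The point should be stated as a possible bias of unknown direction, not as an overstatement of the drug effect.

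**What to change.** 1. Keep the order term as a design term. Delete the claim that it ensures there is no carryover, and draw no conclusion of absent carryover from its p-value.
2. Report the post-washout MFI-20 by sequence, as change from the trial-start score or adjusted for it, with a 95% CI. State that this check is also imprecise, with a half-width of about 7 to 10 points.
3. Keep the planned period-baseline model as primary, and say explicitly that the baseline enters period by period if that is the intention.
4. Add a sensitivity model with the trial-start MFI-20 only. Read the two together, because neither is unbiased under every carryover pattern.

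The cost is a change of wording, one extra table and one extra model, all from data already collected, and a weaker statement about carryover in the report.

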### Sample size

The study was designed to have 80 % power in detecting a 10 point decrease in self-reported fatigue on the MFI after 6 weeks of modafinil treatment with a type I error rate of 0.05 and assuming standard deviation in the patient population of 14. Using previously reported effects of modafinil on fatigue for stroke survivors [10], multiple sclerosis [12] and a Cochrane review [13] a total sample size of 34 is required for a crossover study. Assuming modest participant dropout and study drug compliance, we aim to recruit 36 participants in total. The crossover design reduces the number of participants required and the negative effects of missing data given the small number of dropouts expected [14].

## Discussion

MIDAS seeks to enhance the quality of life in stroke survivors by assisting or resolving stroke-associated fatigue. There are limited interventions available to stroke survivors with scant strong evidence establishing their efficacy. The proposed crossover trial is an ideal study design as the patient disability being examined is already established, meaning that patients can be enrolled for a longer period of time and the fatigue has not spontaneously resolved as has occurred in an earlier time frames post stroke [10]. Additionally, by setting the strict inclusion criterion of an average MFI-20 score of 12 across all domains, we are ensuring that patients have established severe fatigue and are able to rule out milder cases, which may not show a significant change in self-reported scores. Such individual patient selection has been the bedrock of recent stroke trials and is a key to effective therapy delivery. Fatigue is a major health concern for stroke survivors; it reduces their quality of life and limits engagement in rehabilitation activities. An effective therapy may have profound implications for stroke patients’ quality of life.

